### Process evaluation

A process evaluation, according to Hulscher et al. [42], will be performed during and after the intervention to investigate the feasibility of the implementation strategy and to gain insight into the impact of individual implementation activities on guideline adherence. For this purpose, we will document the different implementation activities and the participation level of the health-care providers in order to determine the correlation between the implementation effect (i.e., results of our implementation strategy on guideline adherence) and compliance to the implementation strategy (i.e., degree of implementation). For this, we use the framework of Hulscher et al. for describing the key features of an implementation of change intervention [43]. In this framework, attention is paid to features of the target group, features of the implementers, and the frequency and intensity of intervention activities [43]. Based on this framework, we describe the features of the intervention as performed in detail. The process evaluation will furthermore be based on a questionnaire for the contact persons and a questionnaire for the health-care providers to measure their experience with the implementation strategy. The survey will be emailed to those who have participated in an activity. We will also determine other factors that could have influenced adherence to the perioperative safety guidelines, such as local interventions in the hospitals, audits by the IGZ, other scientific studies in this field conducted in the participating hospitals, and possible confounding factors and barriers for guideline adherence like changing registration systems in the hospitals or merging hospitals.

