In our protocol, hospitals cross over from control to implementation period at three time points (Table 1). A stepped wedge design incorporates data collection in all hospitals at each time point [21,22]. The first time point corresponds to a baseline measurement where none of the hospitals have received the intervention of interest (i.e., multifaceted implementation approach). After the baseline measurement, the first group of hospitals receives the implementation strategy. After the second measurement, the next group of hospitals receives the implementation strategy, and at the third time point, the final group switches from usual care to the implementation phase, so that finally, all included hospitals have received the implementation activities. In this way, comparisons within hospitals and between hospitals will be available, making the design powerful.

**Table 1 Tab1:** **Stepped wedge design with four steps in which ‘C’ represents the control situation and ‘I’ represents the intervention phase**

**Group**	**Measurement**			
	**T0**	**T1**	**T2**	**T3**
**1**	C	I	I	I
**2**	C	C	I	I
**3**	C	C	C	I

In this study, nine hospitals are assigned into three groups of three hospitals. Data collection runs parallel for each hospital. At baseline measurement (T0), all primary and secondary outcomes will be measured per patient (*N* = 50) per hospital. In the interval between T0 and T1, implementation activities will take place in the first group of three hospitals. After the second measurement (T1), the second group of three hospitals crosses over to the intervention phase, while implementation activities continue in the first group and so on. At the final measurement (T3), all hospitals will be in the intervention phase (see Table 1).

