### The intervention

The intervention consists of a multifaceted implementation strategy directed at the cluster. Each group of hospitals will be exposed to the intervention for 4 months. The content of the multifaceted approach is based on 1) scientific literature (systematic review of interventions by Grimshaw et al. [20,26]); 2) expert opinion: prioritizing implementation activities by 24 clinical and implementation experts (RAND modified Delphi method); 3) knowledge and experience of the IMPROVE team regarding the feasibility of the interventions (estimated costs, effort, and time for the hospitals as well as the implementation team). This resulted in a standard package including five activities (Table 2): 1. small educational meetings, 2. audit and feedback (based on local indicator scores and benchmarking, results of surveys on team climate and safety culture, and barriers), 3. structured observation rounds with feedback, 4. integration of the guidelines in local activities and processes, and 5. the use of patient safety cards. A set of six additional activities are offered optional: 1. personal information letter in the mailbox, 2. exchange platform for sharing information between hospitals within a group, 3. scan of the total perioperative process, 4. posters showing details of the perioperative care process, 5. reminder flashes via e-mail, and 6. team training.

**Table 2 Tab2:** **Description of the content of the implementation activities in the IMPROVE standard and additional packages**

**Implementation activities**	**Description**

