**Additional package**	
Personal information letter in the mailbox	Personal information letter to all key disciplines about the (use of the) guidelines.
Exchange platform	This is a platform for the hospitals within a group to exchange their best practices, ideas, and experiences with implementing the guidelines.
Scan of the total perioperative process	A practice scan consisting of five parts:
	-Hospital staff complete an online questionnaire about the perioperative process (via e-mail with a login code)
	-Interviews with hospital staff for more background information (based on remarkable answers in the questionnaire)
	-Structured observation on side
	-Paper report by post (the report contains the findings, a top five of strengths and weaknesses, and recommendations)
	-Feedback meeting to discuss the report
Electronic reminder message	Catchy quote on behalf of an opinion leader within the perioperative process of a hospital. The content is based on the audit results; a recommendation comes in the spotlight which proves to be a bottleneck for the hospital.
Posters	Visual representation of e.g., the stop moments and the perioperative trajectory of the patient, shown as a subway line.
Multi-professional team training	The IMPROVE team facilitates contacts between the participating hospitals and organizations which provide trainings aimed at improving team culture, like crew resource management.

The activities are tailor-made, i.e., the content depends on the analysis of the current performance and guideline adherence (indicator measurement, structured observation of the perioperative care process, and the surveys on team climate and patient safety culture), local barriers in the perioperative setting (barrier analysis), local wishes, and initiatives already realized in the hospital.

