### Analysis

After each measurement period, data are manually checked to identify out-of-range answers, inconsistent or missing data. Because of the hierarchical design (patients nested within hospitals), multilevel linear and logistic regression analysis will be used to compare the outcomes between treatment groups, with age, sex, the American Society of Anesthesiologists (ASA) physical status classification, and socioeconomic status (SES) as covariates. The ASA physical status classification is a five-point scale ranging from ASA 1 (healthy patient) to ASA 5 (moribund patient not expected to survive without surgery, e.g., a patient with a ruptured aortic aneurysm) [41]. Time will be included as fixed effect [22]. The association between guideline adherence and patient outcomes will also be analyzed to determine whether better adherence leads to better patient outcomes. We will use SPSS version 20.0 for data analysis. Significance for all analyses will be set at *P* < 0.05.

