The generalizability of the findings will be high because the study is carried out in a large, heterogeneous sample of nine hospitals across the country. A further strength of this study is the wide scope; we perform measurements at the cluster level and the level of their individual members, i.e., care providers and patients. A questionnaire is sent to the key disciplines to explore all relevant barriers and facilitators to guideline adherence and opportunities for improvement. A better understanding of the barriers and facilitators and a strategy tailored to local circumstances will enhance the implementation of the perioperative guidelines like already mentioned [55,53]. We also carry out a process evaluation to analyze the mechanisms and processes responsible for the outcomes of the effect evaluation; a causal relationship between implementation activities and change in outcomes is difficult to identify because of the presence of confounding factors, like local hospital initiatives to improve patient safety. In case of a multifaceted implementation strategy, the process evaluation is especially important to specify which intervention was most effective [53]. Insight into the implementation process is also relevant for other hospitals that can benefit from the lessons learned. To improve the internal validity, the following actions will be undertaken. To reduce selection bias, the first 50 patients that meet the inclusion criteria are selected from the hospital databases in all hospitals at each measurement point. A possible limitation of the survey investigations is response bias, which will be minimized by sending reminders. Information bias is reduced by having the same researchers (YE and GB) checking the data from the hospital registries and medical records. An independent researcher checks the data entries. An independent statistician will check the analyses. To prevent confounding bias, we study potentially confounding determinants, such as team climate and patient safety culture. To prevent publication bias, the study has been registered in the Dutch register for clinical trials. Additionally, we have installed an external advisory board with the special tasks of checking the design and the integrity of the study and giving feedback.

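### The planned correlation of implementation effect with degree of implementation rests on nine hospitals and a non-randomised dose tailored partly to the same adherence measure; it should be conditioned on that measure and labelled exploratory

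*Protocol article*

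**What the plan says.** The Process evaluation section has two linked aims: "to gain insight into the impact of individual implementation activities on guideline adherence" and, from documented activities and participation, "to determine the correlation between the implementation effect (i.e., results of our implementation strategy on guideline adherence) and compliance to the implementation strategy". It does not state the unit, the scale, or any adjustment for this correlation.

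Three other places bear on it.

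- **Unit of delivery.** Under The intervention: "The intervention consists of a multifaceted implementation strategy directed at the cluster". Under Study design: "nine hospitals are assigned into three groups of three hospitals". Five activities are standard and six are optional, so the amount taken up can differ between hospitals.
- **Tailoring.** After Table 2: "The activities are tailor-made, i.e., the content depends on the analysis of the current performance and guideline adherence". The same sentence also lists local barriers, local wishes and initiatives already in place. The indicator measurement it names belongs to the indicator set that forms the primary outcome.
- **Threshold and use.** The Analysis section states "Significance for all analyses will be set at" P < 0.05, with no exception for exploratory work. The Discussion says that for a multifaceted strategy "the process evaluation is especially important to specify which intervention was most effective".

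**The concern.** Only the timing of cross-over is randomised. How much of the strategy a hospital takes up is not. A relation between uptake and effect is therefore an observational comparison between nine hospitals.

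The design adds a difficulty of its own. Measured adherence helps to shape what a hospital receives, and the same measurement can serve as the before value of its effect. If hospitals with low scores take up more, two things raise their apparent gain even when dose does nothing: a low score is partly chance and tends to rebound, and a low percentage has more room to rise. If well-performing hospitals comply more, the bias runs the other way and a real relation can be hidden.

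The protocol lists other confounders (local initiatives, inspectorate audits, changes in registration systems) but not this one. At stake is the statement that fuller delivery brings better adherence, which other hospitals might take as a lesson.

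**Working it through.** **The plan's own figure.** The protocol gives no figure for this correlation. Its only power figure is at least 0.85 for the primary comparison. The Hussey and Hughes variance (3/3/3 hospitals, four rounds, 50 patients per hospital and round, 50% to 65%, two-sided 0.05, ICC 0.1 to 0.3, normal test) gives 0.92 to 0.98, so that statement holds. It says nothing about a nine-hospital correlation.

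**Precision with nine hospitals (no assumption about direction).**

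- Critical r = t/√(7 + t²) with t(0.975, 7 df) = 2.365: 2.365/√(7 + 5.593) = 0.67.
- 95% CI for an observed r of 0.5: atanh(0.5) = 0.549; SE = 1/√6 = 0.408; 0.549 ± 1.96 × 0.408 = -0.251 to 1.349; back-transformed, -0.25 to 0.87.

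**Regression to the mean alone.** Take the last control round and the first intervention round, the same 15-point gain in every hospital, and stable hospital levels. With s² = 0.25(1 - ICC)/50, τ² = 0.25 × ICC and a correlation ρ between dose and low score, the expected r is ρ√[s²/(2(s² + τ²))].

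- ICC 0.1: √(0.0045/0.059) = 0.28 at ρ = 1.
- ICC 0.3: √(0.0035/0.157) = 0.15 at ρ = 1.

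Simulated means with nine hospitals are 0.26 and 0.14, with P < 0.05 in about 11% and 6-7% of trials. So even full dependence of dose on the score has a modest effect here. Larger figures need hospital levels that drift between rounds: with an assumed autocorrelation of 0.8, 15-19% at full dependence.

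**Ceiling.** A common effect taking 50% to 65% is a log-odds shift of ln(0.65/0.35) = 0.62, an odds ratio of 1.857. A hospital at 80% (odds 4) moves to odds 7.43, which is 88%. That is a gain of 8 points against 15 for the same effect.

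**Both together, no true dose effect.** Inputs from the protocol: nine hospitals, Table 1, 50 patients per round, ICC 0.1 or 0.3 (taken on the log-odds scale), log-odds effect 0.62. Assumed: baseline 50% or 70%, trend 0 or 0.2 log-odds per round, ρ = 0.5 or 0.8 with the last control-round score. Effect = mean of intervention rounds minus mean of control rounds.

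| Scale of change | ρ | Mean spurious r | P < 0.05 |
|---|---|---|---|
| Percentage points | 0.5 | 0.15-0.39 | 7-18% |
| Percentage points | 0.8 | 0.23-0.63 | 10-51% |
| Log-odds | 0.5 | 0.07-0.12 | 6-7% |
| Log-odds | 0.8 | 0.11-0.18 | 7-9% |

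A separate run on the log-odds scale gave 5-9%. Figures near 50% appear only at ρ = 0.8 with a 70% baseline and a trend. Without the trend that case gives about 27%. At ρ = 0 the rate is 5% throughout.

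**Trend.** A linear trend adds the same amount to every hospital's change on the log-odds scale. In rounds, group 1: (1+2+3)/3 - 0 = 2; group 2: (2+3)/2 - (0+1)/2 = 2; group 3: 3 - (0+1+2)/3 = 2. It acts above only by pushing hospitals towards the ceiling. A non-linear trend would not cancel in this way.

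**After adjustment.** Regressing change on dose plus the tailoring-round score brings the false-positive rate back to about 5% on both scales (4-7% across runs).

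**The case against.** The strongest objection is that the article does not specify the analysis criticised. A reader might infer a plain, unadjusted correlation of nine before-after changes. The Process evaluation section says none of this; before-and-after wording appears under Economic evaluation, and the Analysis section plans multilevel models with time as a fixed effect. Groups 2 and 3 also have several control rounds. An article may leave such detail to a fuller document. This stands: the missing detail is not the finding. What remains is what the protocol does fix: a correlation of effect with a non-randomised dose, nine independent hospitals, tailoring on the same measure, and one P threshold for all analyses.

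Second, a reader might infer that low-scoring hospitals receive more. The text says that content, not amount, depends on adherence, alongside barriers, wishes and initiatives, and every hospital is offered the standard package. This stands too: direction and strength are assumptions.

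Third, the large percentages depend on scale. Holding the log-odds effect constant and scoring change in percentage points builds in larger gains for many low scorers. On the scale of the planned logistic model little inflation remains. This also stands.

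Fourth, the Discussion concedes that causality between activities and outcome change is hard to establish. That tempers the reading but does not remove the bias, and the confounders listed do not include tailoring.

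**Conclusion.** The concern holds in a limited form. The certain part is imprecision: with nine hospitals only |r| of at least 0.67 reaches significance, and a moderate observed correlation is compatible with a weak negative or a strong positive relation. The conditional part is bias: if uptake is related to the tailoring score, an unadjusted correlation can create or mask a dose-response. With no dose effect, the false-positive rate is about 5-9% on the log-odds scale and about 7-18% in percentage points at an assumed dose/low-score correlation of 0.5.

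The documents do not support the stronger reading that a spurious dose-response is likely, or that half of such trials would show one. That needs a 0.8 correlation, a 70% baseline, a secular trend and percentage-point scoring together. Nor do they say that advice to other hospitals rests on this correlation alone. The primary comparison and its power are unaffected. This is a minor point, worth considering.

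**What to change.** At hospital level, regress each hospital's change in adherence on its degree of implementation plus its adherence in the round used for tailoring. Preferably express the change on the log-odds scale and adjust it for time. Report the dose slope with its 95% confidence interval. Label the analysis exploratory and exempt it from the general P < 0.05 rule. Do not present an unadjusted correlation as evidence of a dose effect, and add tailoring on measured adherence to the listed confounders.

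The change is to analysis wording only; the indicator data and the record of activities and participation are already planned. The cost is one more parameter with nine hospitals, so a wider interval. Adjustment removes the bias modelled here but does not make dose randomised or the estimate precise.

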### Economic evaluation

Better adherence to the perioperative guidelines may reduce unnecessary perioperative harm such as complications and subsequently welfare losses. To assess the cost implications, an economic evaluation will be conducted that is based on the general principles of a cost-effectiveness analysis. The perspective of this economic evaluation will be a health-care perspective. The input of resources in the implementation strategy will be assessed by collecting volumes of consumed resources and multiplying these by the price of each resource unit (market prices, guideline prices or self-determined prices based on costing methods, i.e., full costing) [44]. The implementation process and consequent costs will be estimated by an activity-based costing (ABC) approach focusing on activities performed with costs accumulated at the activity level(s) of the health-care implementation process [44]. ABC attempts to identify all subprocesses related to the implementation process. Next, the underlying activities (personnel, material, and overhead costs) associated with these subprocesses are identified. Use of ABC concepts facilitates the identification of no value-added activities. The output or consequences of the implementation strategy will be determined by the level of adherence to the perioperative guidelines, measured before and after implementation support.

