## Objective

The aim of this study is to investigate the (cost) effectiveness of a multifaceted approach to implement the perioperative safety guidelines. Our main research question isCan we improve the use of the national perioperative safety guidelines at the hospital and patient levels? In other words, does a multifaceted approach to implement the perioperative guidelines lead to a higher compliance than unsupported implementation?Other research questions are the following:Does the perioperative patient safety (i.e., patient outcomes) improve with better adherence to the guidelines?What are the costs of this implementation strategy and what is the cost-effectiveness at the hospital level?What is the feasibility of this implementation strategy at the hospital level?

In this study protocol, we describe a stepped wedge cluster randomized trial design to evaluate the effect of a multifaceted implementation strategy on guideline adherence and patient safety in Dutch hospitals (research questions 1 and 2). We also describe the economic evaluation (research question 3) and process evaluation (research question 4).

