### Outcome measures

Several outcomes are measured at the hospital (i.e., the cluster) and the patient levels (Table 3). The primary outcome measure is guideline adherence according to the PSIs as defined in the national indicator set. This set comprises nine indicators on the processes and structures of care [18]. Secondary (patient) outcomes are in-hospital complications (with particular attention to postoperative wound infections) and hospital mortality, as well as length of hospital stay (LoHS), unscheduled transfer to the intensive care unit (ICU), non-elective hospital readmission, and unplanned reoperation, which are derived from a maximum period of 30 days after the initial surgery.

**Table 3 Tab3:** **Methods and instruments for measuring the effects of a multifaceted implementation strategy to implement the Dutch national perioperative safety guidelines**

**Outcome variable**	**Data source (type of measurement)**	**Frequency of measurement and sample size per measurement**	**Moment of measurement**	**Unit of analysis**
**Primary outcome** (guideline adherence measured by an indicator set of nine process and structure indicators)				
Completion of the total STOP bundle (seven separate stop moments in the perioperative care process), % patients	Retrospective patient record review in the hospital information systems	4 (T0 (before), T1, T2, T3 (after) measurement) *N* = 1,800	−3 months, +4 months, +11 months and +18 months	Patient
Availability of a protocol on antibiotic use	Short questionnaire on the underlying items of the structure indicators	4 (T0 (before), T1, T2, T3 (after) measurement) *N* = 1	−3 months, +4 months, +11 months and +18 months	Hospital
Timely administration of antibiotic prophylaxis, % patients	Retrospective patient record review in the hospital information systems	4 (T0 (before), T1, T2, T3 (after) measurement) *N* = 1,800	−3 months, +4 months, +11 months and +18 months	Patient
Availability of a protocol on anticoagulant use	Short questionnaire on the underlying items of the structure indicators	4 (T0 (before), T1, T2, T3 (after) measurement) *N* = 1	−3 months, +4 months, +11 months and +18 months	Hospital
Availability of a protocol on responsibilities regarding maintenance of medical equipment	Short questionnaire on the underlying items of the structure indicators	4 (T0 (before), T1, T2, T3 (after) measurement) *N* = 1	−3 months, +4 months, +11 months and +18 months	Hospital

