This study has several strengths and limitations. The major strength of this study is the randomized comparison made possible by the multicenter stepped wedge cluster randomized trial design. In fact, a parallel group cluster randomized trial was not feasible because of the large number of hospitals needed. A (individually) randomized, controlled trial was not possible as all Dutch hospitals have a legal obligation to implement the perioperative safety guidelines; temporarily postponing the implementation of the guidelines would have been unethical. Finally, non-randomized designs such as pre- and post-intervention evaluations are methodologically weaker as they tend to overestimate intervention effects. Another strength of our study is the use of a multifaceted approach consisting of in total 11 different activities, covering six interventions: education, audit and feedback, organizational interventions, team-directed interventions, reminders, as well as patient-mediated interventions, of which most have been shown to be effective in other studies [20,41,47-52]. Combinations of interventions may be more effective than single interventions in changing professional behavior, because a larger variety of barriers for change can be addressed [53]. The effectiveness of a combined strategy is determined by the effectiveness of the separate interventions that make up the strategy and the interaction of the different interventions, which can increase or reduce the total effect. The effect of a combined intervention does not necessarily equal the sum of the effects of the single interventions that comprise it. Different interventions can support each other, so the total effect may be larger than the effects of the interventions separately [53]. However, no specific combination provides a guarantee for success [53]. It seems plausible that combined interventions are only more effective than a single intervention if they address barriers and facilitators that are actually related to professional performance. This emphasizes the importance of a careful documentation of the most important barriers to improvement and the systematic development of implementation strategies as in our study, which is preferred over intuitively selected strategies [53,54]. A multifaceted implementation strategy with activities that are not carefully related to the relevant factors and needs of the target group is an unfocused intervention and likely not effective [53].

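### The economic evaluation takes its effect from adherence before and after support and does not tie it to the time-adjusted stepped-wedge estimate

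*Protocol article*

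**What the plan says.** The Economic evaluation section describes a cost-effectiveness analysis from a health-care perspective. On the effect side it has one sentence: the consequences of the strategy "will be determined by the level of adherence to the perioperative guidelines, measured before and after implementation support". It names no control-period comparator and no adjustment for time, and it does not refer to the model in the Analysis section.

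Other parts of the protocol bear on how that sentence is read:

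- **Objective.** The main question is whether the strategy will "lead to a higher compliance than unsupported implementation". The third question reads "What are the costs of this implementation strategy and what is the cost-effectiveness at the hospital level".
- **Analysis.** Outcomes are compared between treatment groups by multilevel regression, and "Time will be included as fixed effect".
- **Outcome measures, Table 3.** The schedule for adherence is given as "4 (T0 (before), T1, T2, T3 (after) measurement", so T0 is labelled before and T3 after.
- **Study design.** "At the final measurement (T3), all hospitals will be in the intervention phase".
- **Discussion.** The stepped wedge is preferred partly because "non-randomized designs such as pre- and post-intervention evaluations are methodologically weaker as they tend to overestimate intervention effects".

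**The concern.** In a stepped wedge, each hospital's supported measurements all come later in calendar time than its unsupported ones. A before-after difference therefore contains the effect of the strategy plus whatever would have happened to adherence anyway. The design separates the two by comparing hospitals that have crossed over with hospitals that have not, at the same measurement. On Table 3's labels the contrast would be T3 against T0, and at T3 no hospital is still a control.

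Some background movement is plausible on the protocol's own account. The Discussion says all Dutch hospitals are legally bound to implement the guidelines. The Process evaluation section lists local interventions, inspectorate audits and other studies as possible influences on adherence.

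Cost-effectiveness is part of the stated aim. If the sentence is followed as written, the effectiveness and cost-effectiveness questions could rest on two different effects of the same strategy, and only the first would be protected against a calendar trend.

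**Working it through.** The economic section states no figure to reproduce, so the check is how each possible before-after contrast behaves under the design in Table 1.

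**Inputs from the protocol**
- Three groups of three hospitals, measured at T0 to T3. Group 1 is supported from T1, group 2 from T2 and group 3 at T3 (Table 1).
- Measurements at −3, +4, +11 and +18 months, so intervals of 7 months (Table 3).
- Baseline adherence of 50% and an expected effect of 10 to 15 points; 15 is used for the sample size (Power calculation).

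**Assumption.** Without support, adherence changes by b points per interval, linearly and equally in all hospitals. The protocol gives no b, so a range including zero and a negative value is shown.

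**Model.** Expected adherence = 50 + θ × (1 if supported) + b × t, with t = 0, 1, 2, 3 and θ the true effect.

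**Contrasts**
1. *Last measurement before crossover against the first after it.* The two are one interval apart in every group, so the result is θ + 1b.
2. *Mean of supported minus mean of unsupported periods within a hospital.* Group 1: (1+2+3)/3 − 0 = 2. Group 2: (2+3)/2 − (0+1)/2 = 2. Group 3: 3 − (0+1+2)/3 = 2. The result is θ + 2b.
3. *T3 minus T0.* The result is θ + 3b.
4. *Time-adjusted (hospital and period effects).* From T0 to T1, group 1 changes by θ + b and groups 2 and 3 by b. The difference is θ. Fitting all twelve group-by-period cells also returns θ exactly for every trend tried.

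**Apparent effect when the true effect is 15 points**

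| Contrast | Bias | b = −2 | b = 0 | b = 2 | b = 5 |
|---|---|---|---|---|---|
| Adjacent to crossover | 1b | 13 | 15 | 17 | 20 |
| Within-hospital means | 2b | 11 | 15 | 19 | 25 |
| T3 minus T0 | 3b | 9 | 15 | 21 | 30 |
| Time-adjusted | 0 | 15 | 15 | 15 | 15 |

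At b = 2 a true 10 points reads as 12, 14 or 16. At b = 5 a strategy with no effect reads as 5, 10 or 15.

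**Cost per point gained**, if the result is expressed that way, scales as true over apparent effect. For a true 15 points:
- At b = 2: 15/17 = 0.88, 15/19 = 0.79 and 15/21 = 0.71, so it is understated by 12%, 21% or 29%.
- At b = −2: 15/13 = 1.15, 15/11 = 1.36 and 15/9 = 1.67, so it is overstated by 15%, 36% or 67%.

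**Precision.** Take 50 patients per hospital and measurement, within-hospital variance 0.5 × 0.5 = 0.25 and an ICC of 0.1. The Hussey and Hughes formula then gives a standard error of 4.4 points for the time-adjusted effect. T3 minus T0 over nine hospitals has √(2 × 0.25/(50 × 9)) = 0.033, or 3.3 points. The before-after figure looks more precise because it does not pay for estimating the trend.

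**The case against.** The strongest reply is that the sentence names an outcome and when it is measured, not an estimator. Every hospital is measured before and after crossing over. Table 3 uses the same before and after labels for the primary outcome, which the Analysis section does model with time as a fixed effect. Nothing exempts adherence from that model when it enters the economic evaluation, and the Discussion shows the authors knew the weakness of pre-post comparisons. An article may also leave economic detail to a fuller document.

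Part of this stands. A reader might infer that the economic evaluation discards the randomised comparison. The protocol does not say so: that is an inference from the wording, and use of the model estimate is not ruled out. A reader might also infer that a secular improvement will be counted as benefit. The protocol reports no trend. A legal duty does not show that adherence is rising, and the Background says guideline adoption has proved difficult.

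Nor does the protocol fix one multiplier. Pooling all supported against all unsupported cells gives 1.67 intervals (mean t of 2.33 against 0.67). But that contrast includes concurrent controls at T1 and T2, so it is not the within-hospital before-after change the sentence suggests. Finally, unsupported implementation is named as comparator only in the main question. Carrying it to the cost-effectiveness question is reasonable but inferred.

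What does not stand is the claim that this is mere missing detail. The sentence is the protocol's only statement of how the economic effect is obtained, and its ordinary meaning is a before-after change. If the model estimate was intended, the text still needs to say so.

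**Conclusion.** The concern holds as a fault in what is written. The stated effect for the economic evaluation is, on its plain reading, an uncontrolled before-after change. That conflicts with the protocol's own comparator, effect model and view of pre-post evaluations.

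The resulting bias is 1b to 3b, where b is the unsupported change in adherence per 7-month interval. This assumes a linear trend common to all hospitals. Neither the size nor the sign of b can be taken from the protocol, so the numerical examples are illustrations, not estimates. An upward trend is plausible and would flatter the strategy, but that direction is not established.

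The problem is confined to the cost-effectiveness result. The primary comparison of adherence is unaffected.

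**What to change.** In the Economic evaluation section, replace the before-after wording. State that the incremental effect is the time-adjusted intervention-versus-control difference in adherence from the multilevel model in the Analysis section, with its uncertainty carried into the cost-effectiveness result, and that the before-after difference is not the effect input. If the logistic form of the model is used, its estimate has to be turned into a difference in percentage points before costs are set against it.

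This takes a sentence or two and no new data. The Trial status section says no data cleaning or analysis had begun at submission. The price is a result that may be less favourable, if adherence is rising without support, and less precise.
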